**Post-graduate training opportunities:**

The Wellcome-NHMRC studies provide postgraduate training opportunities for each of the core partners involved: NIHRD, MSHR and Sam Ratulangi University in Manado.

These postgraduate training activities are outlined in the original submission endorsed by the Secretary of NIHRD in 2003, and are shared among the submitting partners: ie.

1) NIHRD: has/will have 2 postgraduate students [both ACT studies]

2) MSHR has/will have 2 postgraduate students [one ACT, one arginine study].

3) Universitas Sam Ratulangi (Manado), has had 2 clinical postgraduates working on the previously-approved SEAQUAMAT study as the clinical research requirement for their post-graduate qualification in internal medicine. From 2005, internal medicine trainees will undertake components of the arginine study for their internal medicine research projects.

**Background to NO-arginine studies:**

*How can we reduce mortality in severe malaria?*

Mortality in severe malaria remains between 12-30% despite the best available antimalarials1,2. There are two goals in designing better treatments to reduce mortality in severe malaria: 1) to kill parasites faster and 2) to decrease the excessive inflammation/tissue damage found in severe malaria.

To address the first goal, we are currently conducting a study at RSMM, Timika looking at whether drugs that kill parasites more quickly will reduce mortality [the multi-centre SouthEast Asian trial of artesunate vs quinine (SEAQUAMAT)].

To address the second goal, this arginine-malaria protocol describes the first stages of studies that seek to determine if arginine can act to dampen the excessive inflammation found in severe malaria.

*Arginine and NO:*Arginine: is a naturally occurring amino acid found in plant and animal protein (eg nuts). It is the critical substrate required for the generation of nitric oxide in the body by the action of a family of enzymes the nitric oxide synthases (NOS)3. The constitutively-expressed enzymes NOS1 and NOS3 produce low-level homeostatic neuronal and endothelial NO, whereas in inflammatory states inducible NOS (NOS2) generates high level NO production in a variety of cell types3, including peripheral blood mononuclear cells (PBMCs)4. NO has antimicrobial and immunomodulatory actions during inflammation4-6. Generation of NO from intracellular NOS is critically dependent upon transport of extracellular arginine into cells via the cationic amino acid transporters, CAT1 and CAT2, with the Km for uptake of arginine being 70-150 uM7. In situations of inadequate extracellular arginine availability, NOS generates superoxide instead of NO8-10.

*Arginine: clinical pharmacology:* In healthy humans endogenous arginine is a non-essential amino acid, synthesised from citrulline, which is in turn synthesised from enteral glutamine and glutamate7. However, in acute inflammation such as in sickle cell crisis11,12, severe burns13 and sepsis14, plasma levels of arginine are low and arginine is “conditionally essential” 13,15. Arginine is metabolised by arginases (in hepatocytes and other cell types) to form urea and ornithine, but there is strict segregation of hepatic and plasma arginine pools and only 5% of urea production is derived from plasma arginine7. Arginine is also renally excreted but undergoes almost complete tubular reabsorption16. When exogenous arginine exceeds the renal threshold for tubular reabsorption (eg in supraphysiological dosage), there is additional renal excretion16. The pharmacokinetics of L-arginine are derived from studies of arginine given in large doses only to adults with normal plasma arginine concentrations, where it has been described by non-compartmental analysis16,17. There is apparent evidence for non-linear pharmacokinetics, where a dose-dependent elimination half-life has been reported16,17. The reported half-life for oral and IV arginine ranges from 40-120 minutes (with variability due in part to the non-linearity).16 Reported clearance (CL) ranges from 544-1018 ml/min16. In subjects with normal plasma arginine concentrations, the relationship between pharmacokinetic and pharmacodynamic data (urine NOx and total peripheral resistance) was best described using a linear direct effect model, in which effect was linked directly to L-arginine plasma concentration17.

*Nitric oxide and severe malaria:* Our studies over the last decade have associated NO production with protection from severe malaria. In African children we found an inverse association between malaria disease severity and systemic NO production/monocyte NOS2 expression18. In longitudinal studies, blood monocytes from children with past severe malaria had less NOS activity than those from children with past uncomplicated malaria19. We have also found novel NOS2 polymorphisms associated with increased NO production and protection from severe malaria20. In Papua, we have now recruited over 600 adults with and without severe malaria and shown the same inverse association between disease-severity and NO/PBMC NOS2 in *non-immune* *adults* from *different ethnic groups* in a region of *very different malaria epidemiology* (21and manuscript in preparation; see fig 1). Potential mechanisms for these associations include the ability of NO to decrease pro-inflammatory cytokines22, endothelial cell adhesion molecule expression23, and parasite cytoadherence (our unpublished data) 20. In complementary immunohistochemical studies, other investigators have shown that in contrast to suppression of PBMC NOS expression/systemic NO production, tissue NOS expression is increased in severe malaria24. These tissue studies are unable to directly quantitate NO production. We hypothesise that inadequate arginine levels found in severe malaria limits tissue and monocyte NO production; and that by generating superoxide NOS exacerbates deleterious oxidant stress in severe malaria.

**Figure 1. NO and NOS parameters measured in Papuan adults.** Urinary NOx, PBMC NOS enzyme activity, PBMC NOS2 antigen by immunoblot, and NOS2 mRNA (by RT-PCR) were all inversely associated with disease severity. RHC: rural healthy controls, UHC: urban healthy controls, UM: uncomplicated falciparum malaria, SM: severe malaria

*Hypoargininemia in severe malaria: does this limit NO production and increase mortality?* In Tanzanian children we have now shown that arginine concentrations are inversely associated with disease severity (fig. 2). Moreover, in both univariate (OR 4.0 [95% CI 1.1-15.2]) and multivariate analysis (OR 26.2 [95% CI 1.2-586])], L-arginine level below the median in Tanzanian children with CM was associated with mortality25. In Indonesian adults, the same inverse association between arginine and disease severity is found (fig. 2)

[figure not shown]

Plasma arginine in healthy subjects was not significantly different among different age groups or different ethnic groups25. Our data have shown a mean plasma arginine level for healthy Tanzanian children (n=19) of 122 uM (lower limit of normal 78uM). Mean plasma arginine in American adults (n=23) is 117 uM with lower limit of normal of 59uM25. In Indonesian adults in our previous studies in Jayapura (n=43), mean plasma arginine was 114 uM with lower limit of normal of 54 uM ([name], [name] et al, unpublished data). Hypoargininemia can therefore be defined as levels below 54uM (the lower limit of normal in healthy Jayapura residents). In the Tanzanian data above, there were no differences in fasting or weight-for-age among groups and levels returned to normal by day 3 in adults with severe malaria, despite continuing anorexia. This suggests that our arginine findings are not related to underlying malnutrition or to inadequate dietary arginine ingestion prior to malaria25. The causes of low NO production/monocyte NOS2 and low arginine in severe malaria are likely to be multi-factorial25. In separate studies, we are examining cellular mechanisms of hypoargininemia, including arginase activities and PBMC levels of enzymes involved in synthesis, transport and degradation of arginine. Cytokine responses decreasing NOS2 also diminish factors involved in cellular uptake and biosynthesis of L-arginine.7 Non-plasmodial parasites activate arginases during infection26 but whether *P. falciparum* activates arginases is not yet known. Metabolic turnover may be increased in malaria, similar to that seen in burns13 and sepsis15. ***Irrespective of its cause we hypothesise that hypoargininemia limits NO production in malaria and may contribute to severe disease.***With intracellular NOS activity being critically dependent on adequate circulating L-arginine, and with arginine levels in SM well below the Km for cellular uptake of arginine7 hypoargininemia is likely to result in sub-optimal monocyte, endothelial, and tissue NO production in SM. Moreover, hypoargininemia may enhance8-10 the deleterious oxidative stress described in SM27,28. Strategies to increase NO production (such as L-arginine administration) may improve outcome by ameliorating endothelial dysfunction and decreasing deleterious inflammatory cytokine and oxidative responses. Moreover L-arginine reduces ischaemia-reperfusion injury29, and kills *P. falciparum* *in vitro*30 and *in vivo*31 through an NO-mediated effect. Although hypoargininemia can be defined as levels below 54uM (the lower limit of normal in healthy Jayapura residents), increasing plasma levels within and above the normal range will be expected to increase NO production. However, levels below 600uM (4X Km for CAT transporters) will result in submaximal arginine uptake into cells, and 600uM will therefore be the plasma level for therapeutic target.

*Clinical use of arginine in humans:*L-arginine has been safely used in humans for decades16,32. Arginine has also been well tolerated when given short term (6-30g IV/orally) and long term (6-12 g/day orally) in healthy subjects, and subjects with severe cardiovascular disease and cystic fibrosis with minimal toxicity16,17,32-35. In these diseases, arginine increases NO metabolites and exhaled NO, with improvements in endothelial function, perfusion, symptom scores and exercise tolerance16,17,33,34. Use of 12g IV arginine in sepsis has been shown to improve cardiac output and improve oxygen transport35a. L-arginine therapy corrects the hypoargininemia and impaired NO production found in patients with sickle cell vaso-occlusive syndrome (SCD VOCS),12 a syndrome with endothelial dysfunction and impaired NO production similar to malaria11. Pharmacokinetic data have not been reported in SCD12,36. A randomised trial of L-arginine in SCD VOCS is in progress with no significant adverse effects using 0.1 g/kg IV 8 hrly ([name], personal communication, 2004). Use of enteral arginine supplementation (with or without other “immunonutritional” supplements) in critically unwell intensive care unit patients has been associated with reduced inotrope requirements, higher base excess, reduced risk of nosocomial infection, reduced ventilator days and reduced hospital stay,37-40,41. Beneifts were particularly noteworthy in septic ICU patients41. Use of oral arginine in patients with tuberculosis showed an increase in weight gain, reduced sputum conversion time and reduced symptoms compared to controls41a. Arginine is off-patent and available as an inexpensive, generic, GMP-standard product for human use. For potential adverse effects of arginine (in a malaria context) see “Study 2” below.

**3. Rationale for the Arginine-NO studies:**

There is a need for novel adjunctive antidisease therapies to reduce the unacceptably high case-fatality of severe malaria (SM) further1,2. Irrespective of its cause, hypoargininemia likely limits NO production and is associated with death in cerebral malaria25. Our NO-arginine-malaria studies and the results of arginine trials in related diseases suggest that arginine may have potential for therapeutic use in malaria. L-arginine is commercially available as an off-patent product for human use, is inexpensive, and has been widely used worldwide with little toxicity despite supra-physiological intravenous dosing as a diagnostic pituitary function test and administration in other human diseases36 (see also “clinical use of arginine in humans” above). It is important to determine whether arginine administered to malaria patients increases NO production, reduces measures of oxidant stress and has physiological effects at the doses proposed: this has implications for understanding the pathophysiology of severe malaria, as well as therapeutic implications. Arginine pharmacokinetics have not yet been described in hypoargininemic states such as uncomplicated and severe malaria. Our proposed safety, pharmacokinetic-pharmacodynamic and efficacy studies in uncomplicated malaria will be the first steps in cautiously determining if exogenous arginine administration has therapeutic potential in malaria.

**4. Our aims** are to:

4.1 Determine the natural history of recovery of plasma arginine levels and our pharmacodynamic measurements in uncomplicated and severe malaria.

4.2 Determine the pharmacokinetics, pharmacodynamics and safety of L-arginine in uncomplicated malaria**.**

4.3 Determine preliminary effects on biomarkers of outcome in uncomplicated malaria.

4.4 Establish the relationship between malaria disease severity and those measures used to monitor pharmacodynamic effects: exhaled NO, plasma/urine NO metabolites, oxidant stress, brachial artery dilatation, doppler evaluation of microvascular blood flow, physiological deadspace.

**We will test the following hypotheses arising from our work:**

Low plasma arginine levels in uncomplicated malaria limits nitric oxide (NO) production in malaria. Arginine supplementation is safe, restores plasma arginine levels to normal, increases systemic and exhaled NO production, reduces oxidant stress, and improves a number of physiological measures of relevance to malaria (including vascular endothelial function and physiological deadspace)

**5. Study Design:**

**Study site:**

Patients will be enrolled at RS Mitra Masyarakat (RSMM), Timika, Papua, Indonesia. A malaria research collaboration is already established with this hospital as part of the MOU between NIHRD, RSMM, Regional Ministry of Health and MSHR. It is the site of our recent NO-malaria studies, lung-malaria and SEAQUAMAT severe malaria studies all of which have involved capacity building and clinical research training to local investigators.

RSMM has approximately 200 malaria admissions per month The hospital has a well-equipped clinical research ward attached to its high dependency unit, where the arginine administration studies will take place.

**Overview:**We will determine pharmacokinetics, pharmacodynamics, safety, appropriate dosing and preliminary efficacy of L-arginine in uncomplicated malaria: the arginine studies will be comprise three stages: studies 1 and 2 will be undertaken in parallel, followed by stage 3.

1. *Natural history study: time course of recovery of hypoargininemia (and pharmaco-dynamic measures) in uncomplicated and severe malaria:*
2. *Pilot safety, pharmacokinetic and pharmacodynamic study of exogenous arginine in uncomplicated falciparum malaria*
3. *Randomised concentration controlled trial, safety and pharmacokinetic study in uncomplicated malaria*

**Goal:** to be able to optimize the arginine dose to achieve the best outcomes possible in malaria.

**Patients:**

*Study 1:*

*Uncomplicated falciparum malaria (UF)*:

Inclusion criteria:

1. age 18-60 years
2. *P. falciparum* parasitemia (1,000-100,000 parasites/ul).
3. Clinical syndrome consistent will malaria associated with documented fever (axillary temperature  38oC) or self-reported history of fever in the last 48 hours with no other cause present
4. Time of commencement of quinine known
5. An indication for hospital admission [eg relative cannot stay at home to look after them or supervise their treatment at home, one episode of vomiting (but not repeated episodes of vomiting)], but not having the warning signs or severe malaria criteria in “exclusion criteria” below
6. Informed consent obtained

Exclusion criteria:

1. pregnancy or lactation
2. mixed infection with *P. falciparum* and *P. vivax*
3. warning signs ofaltered mental state and inability to sit unaided
4. features of severe/complicated malaria2 (see “severe malaria” below)
5. diabetes
6. systolic BP <100 mmHg
7. serious underlying diseases (cardiac, hepatic, kidney and lung)
8. malnutrion
9. other infection
10. concurrent therapy/medication including: anti-TB, Asthma drugs.

All UF subjects will be treated with quinine as per standard RSMM practice. Height and weight will be documented in all subjects.

*Severe malaria (SM)*, defined by modified WHO criteria42:

Inclusion criteria:

1. age ≥ 18 years
2. Informed consent obtained
3. Time of commencement of quinine known
4. any level of *P. falciparum* parasitemia, and one or more of the following criteria:
   1. acute renal failure (creatinine >265umol/L)
   2. hyperbilirubinemia (total bilirubin > 50 umol/L) with either renal impairment (creatinine > 130umol/L) or parasitemia of >100,000 parasites/uL
   3. blackwater fever
   4. hyperparasitemia (>10% parasitised red cells)
   5. cerebral malaria (Glasgow coma score <11)
   6. Hypoglycemia
   7. Respiratory distress (RR>32)
   8. Acidosis: venous bicarbonate < 15 mmol/L.
   9. Shock: systolic BP <80 mmHg with cold peripheries

Exclusion criteria:

1. severe anemia (Hb <6 mg/dL) and
2. pregnancy or lactation.

Clinical care, and monitoring will be as per standard national, RSMM and WHO protocols2.

*Studies 2 and 3: Uncomplicated falciparum malaria (UF)*:

Inclusion criteria:

1. age 18-60 years
2. *P. falciparum* parasitemia (1,000-100,000 parasites/ul).
3. Clinical syndrome consistent will malaria associated with documented fever (axillary temperature  38oC) or self-reported history of fever in the last 48 hours with no other cause present
4. Commenced oral quinine ≤18 hours prior to scheduled commencement of arginine
5. An indication for hospital admission (eg relative cannot look after/supervise treatment at home **but not having any warning signs or severe malaria criteria in “exclusion criteria” below)**
6. Informed consent obtained

Exclusion criteria:

1. pregnancy or lactation
2. mixed infection with *P. falciparum* and *P. vivax*
3. Warning signs ofaltered mental state and inability to sit unaided
4. features of severe/complicated malaria2 (see “severe malaria” Study 1 above),
5. diabetes
6. systolic BP <100 mmHg
7. serious underlying disease (cardiac, hepatic, kidney)
8. initial iSTAT test showing any of the following values:
   - 1. glucose < 4 mmol/L
     2. K+ ≥ 4.2 meq/L
     3. Cl- > 106 meq/L
     4. HCO3- < 20 meq/L
9. known allergy to L-arginine
10. concurrent therapy with any of the following medications:
    - 1. spironolactone,
      2. oral nitrates,
      3. phosphodiesterase inhibitor (eg sildenafil [Viagra])
      4. alpha-blocking antihypertensive agents (eg prazosin)
      5. L-arginine

All UF subjects will be treated with quinine as per standard RSMM/Depkes protocols and will commence arginine within 18 hours of commencing quinine. Height and weight will be documented in all subjects.

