**1. Wellcome Trust-NHMRC studies:**

In 2003, NIHRD and MSHR submitted a joint funding submission to The Wellcome Trust (a UK-based medical charity) and NHMRC in response to their call for submissions for their inaugural International Collaborative Research Grants Scheme. The submission was endorsed by the Secretary of NIHRD and the Director of MSHR. Over 140 submissions were received, and these were scrutinized by an international scientific panel for both scientific merit and potential for translation into improvements in health. The NIHRD-MSHR submission was one of only 11 that were successful. There were two components to the submission: The first involved comparative studies of artemisinin combination therapy in Timika, and whether widespread deployment will reduce malaria morbidity and mortality in a medium-transmission region. The ACT comparative studies have been approved by the Ethics committee in Jakarta and the studies have commenced in Timika. The second component of the Wellcome-NHMRC submission is an extension of the NIHRD-MSHR nitric oxide studies. For the first time we will extend the findings from our pathophysiology studies to test whether a simple intervention with arginine, a natural product found in food protein, can increase nitric oxide production and reduce malaria morbidity when used as adjunctive treatment for malaria.

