**Study 1**

***Time course of recovery of plasma arginine, NOS cofactors and pharmacodynamic measures in uncomplicated and severe malaria:*** Our data on existing cryopreserved plasma in Indonesian adults indicate that plasma arginine levels in severe malaria have returned to normal by day 3 (fig. 2), however the rate of recovery of arginine levels in uncomplicated and severe malaria is not known. In 20 patients with UF and 20 with SM (defined above), we will measure serial measurements of plasma arginine to determine the natural history of recovery of plasma arginine concentrations in patients with malaria, and the natural history of recovery of the pharmacodynamic measurements to be used in stage 2.

*Clinical measures.* Vital signs (pulse rate, BP, temperature, respiration rate), and a standardised clinical assessment (symptom/signs listed in Table footnotes) will be serially monitored over 24-72 hours (see table 1). ECG will also be monitored from 0-240 mins.

*Sampling regimen and amino acid measurements:*

1. Blood: An additional venous cannula for sampling will be placed at the time of enrolment. At the time of cannula insertion we will take 10ml heparinised baseline blood (processed as per enrolment in NO Study II SOP for heparinised blood).

Subsequent sampling regimens:

2 ml (in heparinised blood) collected on up to five further occasions over 48-72 hours depending on clinical need for hospitalisation (see example of sampling schedule in table 1). **Of particular note, for the pharmacokinetic-pharmacodynamic modeling proposed in studies 1 and 2, it is advantageous for serial blood samples/measures to be collected at varied time points.**

Total amount of blood taken: ≤20 ml.

Plasma will be cryopreserved at -70ºC for later quantitation of the following:

- arginine, its metabolites and related amino acids by HPLC25 (Shimadzu) using our established methodology (figure 2).
- NO metabolites (nitrate plus nitrite) using Greiss reagents as we have performed previously, and measures of oxidant production (including oxidized glutathione).
- CK, LFTs, lactate, urea, creatinine and the electrolytes required for study 2 below.
- sICAM-1 and other biochemical measures of endothelial activation

See footnotes to table 1 for where each test will be measured.

**Please see Appendix 2 for details of the type of specimens, type of tests and location of where the tests will be performed.**

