**Footnotes for tables 1 and 2:**

Arginine infusion (Table 2): from time 0-30 mins

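### Time on treatment is counted from quinine alone, so an antimalarial taken earlier in the same illness is neither asked about, excluded nor adjusted for

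*Combined protocol and SAP*

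**What the plan says.** The eligibility lists are under 5. Study Design, Patients.

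- **Study 1, uncomplicated falciparum (UF) and severe malaria (SM):** the only treatment-timing item is "Time of commencement of quinine known". There is no upper limit on elapsed time.
- **Studies 2 and 3:** the timing item is "Commenced oral quinine ≤18 hours prior to scheduled commencement of arginine".
- **Drug exclusions:** Study 1 UF excludes "concurrent therapy/medication including: anti-TB, Asthma drugs". Studies 2 and 3 exclude "concurrent therapy with any of the following medications", followed by a closed list of five: spironolactone, oral nitrates, phosphodiesterase inhibitors, alpha-blockers and L-arginine. The SM list has no drug item.
- **Other entry conditions:** UF patients need 1,000 to 100,000 parasites/ul, and either documented fever or a self-reported history of fever in the last 48 hours.
- **Adjustment:** the Study 1 Interpretation paragraph compares recovery times controlling for admission parasitaemia, age, sex and duration of fasting. The Study 2 modelling paragraph mentions covariates only in general terms, with age as the example.
- **Clock:** for Study 2 the table footnote reads "Arginine infusion (Table 2): from time 0-30 mins". For Study 1, "An additional venous cannula for sampling will be placed at the time of enrolment", and the 10 mL baseline sample taken then is the time 0 column of Table 1.

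**The concern.** A requirement to know when treatment began, or to cap the time since it began, evidently serves to place each patient on the recovery curve. Counted from quinine alone, it does not do so for a patient who took a different antimalarial first. If the earlier drug had some effect, such a patient enters further along than the record shows, with higher arginine at baseline and an apparently shorter recovery.

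The natural rate of arginine recovery is the quantity Study 1 exists to estimate. It also enters the pharmacokinetic-pharmacodynamic model as the zero-dose data. Study 1 further compares admission values between UF, SM and vivax malaria, 50 per group, and the vivax group takes over the UF definition apart from the parasite. If prior treatment is more common in one group, that comparison is biased; if it is equally common, it adds noise. In Study 2 the three dose cohorts of 10 are filled in sequence without randomisation, so nothing balances prior treatment between doses.

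**Working it through.** The plan gives no figure to reproduce. The check is a reading of the criteria, followed by scale calculations under stated assumptions.

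**1. Can a pre-treated patient pass?** Take a UF patient who began another antimalarial a day before quinine, now has at least 1,000 parasites/ul, and reports fever within 48 hours.

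- Parasitaemia: met.
- Fever: met on history, even if the patient is now afebrile.
- Quinine timing: met, because the count starts at quinine.
- Drug exclusions: the Studies 2 and 3 list contains no antimalarial. The Study 1 UF item is open-ended but covers concurrent drugs, not a course already replaced.

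No criterion on prior treatment stops entry, and no listed covariate records the extra day.

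**2. How large is the timing error?** Study 1 states that plasma arginine in severe malaria is back to normal by day 3, which Table 1 places at about 72 h, and that the rate of recovery is not known. The unrecorded offset is assumed. Share of recovery = offset / 72:

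| Assumed offset | Share of 72 h |
| --- | --- |
| 6 h | 6/72 = 8% |
| 12 h | 12/72 = 17% |
| 24 h | 24/72 = 33% |
| 48 h | 48/72 = 67% |

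This assumes straight-line recovery and an earlier drug as effective as quinine. Because day 3 is when levels were found normal, recovery may be faster, and the share then larger. The 72 h figure comes from severe malaria; no figure for UF is given.

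**3. How likely is a Study 2 cohort to contain such a patient?** With pre-treated share p (assumed), P(at least one of 10) = 1 − (1 − p)^10:

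- p = 10%: 1 − 0.9^10 = 65%
- p = 20%: 1 − 0.8^10 = 89%
- p = 30%: 1 − 0.7^10 = 97%

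**4. What remains in Study 3?** The provisional size is about 20 per group. For two independent binomial counts with n = 20 and the same p, the chance that the arms differ by 3 or more pre-treated patients is 18%, 32% and 39% at p = 10%, 20% and 30%. For context, 80% power at two-sided 0.05 (both assumed, as the plan states neither) requires (1.960 + 0.842) × √(2/20) = 0.89 SD, so there is little room for added noise.

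**5. Does it move the Study 3 dose?** The target is about 600 uM. In healthy Indonesian adults the mean is 114 uM and the lower limit of normal 54 uM. A 24 h offset moves endogenous arginine by (24/72) × (114 − 54) = 20 uM, or 20/600 = 3% of target. Even starting from zero it is (24/72) × 114 = 38 uM, or 6%. A 48 h offset doubles these to 40 and 76 uM, 7% and 13%.

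**The case against.** **Parts that stand.** The documents give no frequency of pre-treatment. A patient with a day of effective therapy must still have 1,000 parasites/ul to enter, which limits the numbers. The case report form is cited but not in the documents and may record earlier drugs. Each Study 2 patient's own arginine is measured before infusion, the model estimates between-subject variability, and the Data Monitoring Committee reviews the Study 3 dose. These points limit the consequences. They do not supply a criterion or a covariate, and a form entry alone would neither exclude nor adjust.

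**Stronger readings the documents do not support.**

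- *Time zero is false.* A reader might infer this from the quinine criterion. Scheduled time 0 is the infusion in Study 2 and the enrolment baseline in Study 1, and both remain right in a pre-treated patient. What is missing is elapsed time since first treatment.
- *Trials at the site show that pre-treated patients will enter.* The Background says "we are currently conducting a study at RSMM, Timika looking at whether drugs that kill parasites more quickly will reduce mortality", but that artesunate-quinine trial concerns severe malaria and cannot reach UF patients. It also says "The ACT comparative studies have been approved by the Ethics committee in Jakarta and the studies have commenced in Timika", which names Timika, not the study hospital. Nothing describes patients switching from those regimens to quinine.
- *The quinine criterion removes a large share of severe patients.* That would need co-enrolment in the artesunate trial and a known allocation ratio. The plan states neither.
- *The Study 3 comparison is biased.* Randomisation protects it in expectation.

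**Conclusion.** The gap is real and goes beyond missing detail: as written, the 18 h limit does not bound time on treatment for a patient treated before quinine, and no planned adjustment corrects for it. It bears mainly on the Study 1 recovery curves and admission comparisons and on the non-randomised Study 2 cohorts. In Study 3 it leaves noise and possible chance imbalance in fever and parasite clearance times. The effect on the 600 uM dosing target is small, about 3% to 6% for a 24 h offset.

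The size per affected patient (8% to 67% of a 72 h recovery) depends on an assumed offset of 6 to 48 h, a straight line and a severe-malaria time scale. The number of affected patients cannot be known from the documents. The point should be corrected before enrolment, but it does not invalidate the design.

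**What to change.** 1. **UF criteria.** Count the existing 18 h limit (Studies 2 and 3) and the known-start requirement (Study 1) from the first dose of any antimalarial for this illness. Ask at screening, and record drug and time. Leave the scheduled time 0 unchanged. A fixed washout of several days is not needed, and the documents give no basis for choosing its length.
2. **Analysis.** Add time since first antimalarial to the Study 1 adjustment list and to the pharmacokinetic-pharmacodynamic covariates. Add a sensitivity analysis without pre-treated patients.
3. **Study 1 SM.** Let the 30 admission-only patients qualify on a known time of first antimalarial, whichever drug they receive, since only admission values are measured. Keep the serial recovery curve to quinine-treated patients.

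The cost is one screening question, a few words in the lists, and a few pre-treated UF patients turned away. With approximately 200 malaria admissions a month at the hospital, recruitment should absorb this. Self-reported drug histories will be imperfect, so the covariate reduces the error without removing it.
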